#### 7.6 Human Factors Evaluations

##### 7.6.1 Questionnaires

Associations between questionnaire scores and T1D variables, such as residual C-peptide secretion, HbA1c, episodes of serious hypoglycemia, glycemic variability, and DKA at each time point and over time will be examined. The analysis will be performed by [name].

##### 7.6.2 Quality of Sleep Assessment

The Pittsburgh Sleep Quality Index (PSQI) and actigraphy data will be used to calculate mean total sleep quality score, sleep duration, time in bed, sleep disturbance (including wake after sleep onset and number of awakenings), latency, efficiency, quality, and daytime dysfunction. The analysis will be conducted by [name].

##### 7.6.3 Qualitative Interviews

The qualitative interviews will be analyzed thematically using the method of constant comparison. The analysis will be conducted by [name].

##### 7.6.4 Focus Groups

Focus groups will take place at 24 months with participants and their parents (8-12 participants per group, from both study arms) at each of the study sites. A script of open ended questions will be used to gather feedback and reactions to study recruitment and randomization, study support systems, and the closed loop system. There will also be time for discussion of content raised by participants. The analysis will be conducted by [name].

#### 7.7 Health Economic Evaluation

A health economic evaluation based on short term clinical results and costs of interventions will be conducted by [name]. The analysis will project costs and clinical benefits into longer term endpoints.

### 8 Safety Analyses

A reportable adverse event for this protocol is any untoward medical occurrence that meets criteria for a serious adverse event or any unanticipated medical occurrence in a study subject that is study or device-related. Device deficiencies that could have led to a serious adverse device effect will also be reported.

F:\user\Diabetes Studies\JDRFAPP\Protocols\APCam Newly Diagnosed - CLOuD\Statistics\Electronic Binder\4. SAP\CLOuD SAP V2.0 4-4-19.docx

Safety data including severe hypoglycemic events and ketone-positive hyperglycemia will be tabulated for all subjects, including drop-outs and withdrawals, irrespective of whether CGM data are available and irrespective of whether closed loop was operational. For each event, the following information will be reported:

- Onset date of the event
- Resolution date of the event
- Duration of the event (in days)
- Description of the event
- Intensity of the event
- Seriousness of the event
- Whether the event was related to the study treatment
- Whether the event was related to the study procedure
- Whether the event was related to the study device
- Whether the event required treatment
- Outcome of the event

Separate listings will be provided for pre-randomization and post-randomization adverse events. For post-randomization events, the subject's treatment group will be included in the tabulation.

For the purpose of analysis, a severe hypoglycemic event will be defined as an event requiring assistance of another person actively to administer carbohydrate, glucagon, or other resuscitative actions. These episodes may be associated with sufficient neuroglycopenia including temporary impairment of cognition, incoherent, disoriented, and/or combative behavior, seizure, or coma. If plasma glucose measurements are not available during such an event, neurological recovery attributable to the restoration of plasma glucose to normal is considered sufficient evidence that the event was induced by a low plasma glucose concentration.

Summary statistics and analysis of safety outcomes will consist of the following:

1. Number of episodes of severe hypoglycemic events per subject and incidence rate per 100-person years
2. Number of subjects with severe hypoglycemic events
3. Number of episodes of DKA events per subject and incidence rate per 100-person years
4. Number of subjects with DKA events
5. Number of any other adverse events reported per subject
6. Number of any other serious adverse events reported per subject

Comparison of safety outcomes between the two treatment groups only include those events occurring on or after randomization until the last visit date or the last event date (whichever is later). Comparisons will be performed at 12 and 24 months post diagnosis of T1D. For subjects who continue into the extension phase, comparisons also will be done at 36 and 48 months.

For the binary safety outcomes listed above, a repeated measures logistic regression model will be used to compare treatment arms. For the count outcomes and the incidence rates, a Poisson regression model will be used. All models will adjust for site as a random effect. Additionally,

F:\user\Diabetes Studies\JDRFAPP\Protocols\APCam Newly Diagnosed - CLOuD\Statistics\Electronic Binder\4. SAP\CLOuD SAP V2.0 4-4-19.docx

the models for the DKA outcomes will adjust for presence of a DKA event at diagnosis. A p-value <0.05 will be used to declare statistical significance.

Any other adverse events will be listed by treatment group.

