### 11.3.2 Hypoglycaemia and hyperglycaemia

Subjects with type 1 diabetes have a pre-existing risk for hypoglycaemia and hyperglycaemia. Potential risks are:

- Risk of mild to moderate hypoglycaemia and associated symptoms such as sweating, trembling, difficulty thinking and dizziness. There is also a rare risk of severe hypoglycaemia when conscious level is altered, needing help from a third party to correct the hypoglycaemia. These risks are pre-existent in any patient with type 1 diabetes and the study objective is to develop systems to minimise these risks

- Risk of possible mild to moderate hyperglycaemia similar to the risk that a subject with type 1 diabetes experiences on a daily basis
- Risk of hyperglycaemia leading to diabetic ketoacidosis (DKA). This risk is pre-existent in any patient with type 1 diabetes.

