#### 14.5 Statistical methods

The respective values obtained during the 24-month randomised interventions and the extension phase, contrasting the closed loop against usual care will be compared using an ANCOVA model adjusting for gender, presence or absence of DKA, age and baseline log(C-peptide+1). Primary and secondary analyses will also be conducted to adjust for the baseline C-peptide and HbA1c levels, and by age, BMI, z-score, gender and race/ethnicity, as appropriate. A centre-effect will be explored in the analyses by evaluating for interaction between centre and treatment group on outcome. Secondary per protocol analyses will be conducted. Analyses will be carried out at month 24 and month 48 post-diagnosis.

205761\_Protocol\_V8.0\_10 September 2019

Primary analysis will be a single comparison and no attempt will be formally made to control the overall type I error rate for the secondary outcomes. For non-normally distributed parameters transformation or nonparametric analyses will be used. A 5% significance level will be used to declare statistical significance for the primary comparison.

Severe hypoglycaemic events and ketone-positive hyperglycaemia will be tabulated in each treatment group, which will be compared using repeated measures logistic regression (generalised estimator equation).

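### The safety comparisons of severe hypoglycaemia and DKA name no test and no sparse-data fallback, so if one arm has no events the reported p-value depends on an unstated choice

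*Combined protocol and SAP*

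**What the plan says.** SAP section 8 lists two per-participant binary safety outcomes: "Number of subjects with severe hypoglycemic events" and "Number of subjects with DKA events". For these, "For the binary safety outcomes listed above, a repeated measures logistic regression model will be used to compare treatment arms". For episodes, "For the count outcomes and the incidence rates, a Poisson regression model will be used". It adds that "All models will adjust for site as a random effect" and that "the models for the DKA outcomes will adjust for presence of a DKA event at diagnosis". Significance is declared at p<0.05 (two-sided under SAP 5.1). Comparisons are made at 12 and 24 months, and at 36 and 48 months for those in the extension.

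Protocol 14.5 covers severe hypoglycaemia and ketone-positive hyperglycaemia, "which will be compared using repeated measures logistic regression (generalised estimator equation", that is, a marginal model rather than the SAP's random-effect model.

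Neither document names the test, sets a minimum number of events, or says what happens if an arm has none. The transformation and nonparametric fallbacks in SAP 5.1, 6.2 and 7.3 are triggered by skewed values or residuals, which is a different problem.

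On frequency, protocol 11.3.2 says only: "There is also a rare risk of severe hypoglycaemia when conscious level is altered". It gives no frequency for DKA.

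**The concern.** These are the between-arm tests of the trial's two named harms. When one arm has no participant with an event, the data are separated: the maximum-likelihood log odds ratio has no finite value, and software stops at an arbitrary large number. What follows depends on how the p-value is computed. A model-based Wald test divides by a standard error in the hundreds or thousands and gives p near 1. A sandwich-variance GEE gives a small standard error and an absurdly small p. The same table can therefore be reported as no evidence of a difference or as overwhelming evidence, in either arm's favour, with nothing in the plan to settle which.

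The DKA model's extra covariate thins the data further. The term 'repeated measures' is also undefined: the number of participants with an event gives one yes/no per participant at each comparison time, and the SAP does not say what is repeated.

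**Working it through.** **Inputs.** 48 per arm (SAP 3); seven sites (protocol 9.1); two-sided 0.05 (SAP 5.1 and 8). The plan states no power or event rate for the safety comparisons, so it has no figure of its own to reproduce beyond the arm size. For that, a two-sample t calculation with effect 0.126, SD 0.18 and 90% power gives 43.87, so 44 per group as stated, and 44 × 1.1 = 48.4, consistent with the stated 48. All event risks below are assumptions.

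**One table worked through: 0/48 v 6/48.**
- Fisher's exact: 2 × C(48,6)/C(96,6) = 2 × 0.01324 = 0.026.
- Logistic, likelihood ratio (no site effect): 2 × (−18.085 + 22.444) = 8.72 on 1 df, p = 0.003. With the random site effect, p = 0.003 again.
- Random-site logistic, Wald: log odds ratio −18.0, SE 3083, z = −0.006, p = 0.995.
- Plain logistic, Wald: −21.6 / 11469, p = 0.998.
- Poisson, Wald: −22.4 / 17985, p = 0.999.
- Firth penalised logistic: log odds ratio −2.70, penalised likelihood-ratio p = 0.011.

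**Other tables with an empty arm (0/48 v k/48), p-values.**

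| k | Fisher | Firth | Random-site Wald | Random-site likelihood ratio | Poisson Wald |
|---|---|---|---|---|---|
| 1 | 1.0 | 0.47 | 0.996 | 0.24 | 0.999 |
| 3 | 0.24 | 0.11 | 0.97 | 0.039 | 0.999 |
| 6 | 0.026 | 0.011 | 0.995 | 0.003 | 0.999 |
| 8 | 0.006 | 0.002 | 0.97 | 0.0006 | 0.999 |
| 10 | 0.001 | 0.0004 | 0.97 | 0.0001 | 0.999 |

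GEE was fitted with one record per participant. With model-based variance it gives p = 0.999 throughout. With sandwich variance it gives p below 1e-90 at every k from 1 to 10; at k = 1 the estimate is −20.7 with SE 1.02.

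**How often an arm is empty, at an assumed equal risk r.** P(at least one empty arm) = 1 − (1 − (1 − r)^48)².
- r = 1%: (1 − r)^48 = 0.617, giving 85%
- r = 2%: 0.379, giving 61%
- r = 3%: 0.232, giving 41%
- r = 5%: 0.085, giving 16%
- r = 10%: 0.006, giving 1%

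These include 0 v 0 (0.379² = 14% of trials at r = 2%) and 0 v 1 to 5, where Fisher's test is not significant either (0 v 5: p = 0.056).

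**How often an empty arm faces six or more events, at assumed unequal risks.** With 1% in one arm, the chance is 0.99^48 × P(Bin(48, r₂) ≥ 6):
- r₂ = 5%: 0.617 × 0.032 = 2%
- r₂ = 8%: 0.617 × 0.183 = 11%
- r₂ = 10%: 0.617 × 0.347 = 21%
- r₂ = 15%: 0.617 × 0.746 = 46%

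At 1% v 10% Fisher's power is 25%, of which 21 points come from tables with an empty arm. At 1% v 15% it is 60%, of which 46 points do. So at these risks, most of the imbalances that an exact test could detect fall in tables where a Wald test shows nothing.

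**The case against.** A reader might infer that the planned model cannot test an empty-arm result, and that the trial would therefore report no difference. The documents do not support that. They name a model and not a test: a likelihood-ratio test from the same random-site model gives 0.003 at 0 v 6, and the protocol's GEE with sandwich variance errs the opposite way. What stands is that the result is unspecified. Nor is the ordinary likelihood-ratio test a full remedy, since at 0 v 3 it gives 0.039 against Fisher's 0.24.

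A reader might also take the equal-risk percentages as the chance of missing a real harm. They are not: with equal risks there is no imbalance to miss, and 0 v 6 or more then occurs in only 0.03%, 0.14% and 0.5% of trials at 2%, 3% and 5%. The 46% figure needs 1% v 15%, which fits poorly with a rare event. The word 'rare' in protocol 11.3.2 is tied to altered consciousness, while the analysis definition in SAP 8 is worded more broadly.

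The imbalance would not be hidden. SAP 8 tabulates events with treatment group, SAP 11 has reportable adverse events reviewed unmasked every six months, and the stopping criteria in protocol 9.17 do not use this p-value. Protocol 14.8 lets deviations from the statistical plan be recorded and agreed, but a method chosen after the counts are seen is what pre-specification is meant to avoid.

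Finally, it is too strong to say that nothing is repeated. Event status by reporting period could be the repeated measure; the SAP does not say so.

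**Conclusion.** The concern holds in this form: for the trial's two named harms, SAP 8 commits to a significance test whose result is undefined when one arm has no events. Depending on an unstated choice, 0/48 v 6/48 gives p near 1 or 0.003 (Fisher 0.026), and the protocol's GEE can give p below 1e-90 for a single event. The Poisson models in the same section do not rescue the comparison, because their Wald test fails in the same way.

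The algebra of separation needs no assumption. How often it would matter does: an empty arm is likely if the risk per participant is about 1% to 3% and unlikely at 10%. A clear imbalance with an empty arm ranges from 2% to 46% of trials over the assumed contrasts of 1% v 5% to 1% v 15%. The damage is confined to the reported estimate, interval and p-value. This should be corrected, but it does not threaten participant oversight, and no clinical management is affected.

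**What to change.** In SAP 8, analyse the two per-participant binary outcomes at each reporting time by a method valid for sparse data:

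- either Fisher's exact test (or an exact test stratified by site), with an exact or score confidence interval for the risk difference;
- or Firth penalised logistic regression with a profile-likelihood p-value and interval, adding DKA at diagnosis in the DKA model.

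At minimum, make one of these the stated fallback when an arm has no events or few, with 'few' given as a number. Give the Poisson models a matching fallback: an exact conditional comparison of rates, or a penalised or likelihood-ratio test. The penalised or exact form is preferable, given how the ordinary likelihood-ratio test behaves at small counts in the logistic model. Either define what is repeated in 'repeated measures' or drop the term, and bring protocol 14.5 into line with the SAP.

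The cost is a few sentences and standard software, with no new data. Exact tests are slightly conservative, and the unadjusted and Firth options give up the random site effect.

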### 13 Multiple Comparisons/Multiplicity

In this study, the primary analysis will be a single comparison of C-peptide AUC between the two treatment arms. The primary outcome will be tested at  $\alpha=0.04$ .

For the secondary analyses, the following outcomes will be considered key endpoints:

- Percent time in the target range (3.9-10.0 mmol/L)
- HbA1c
- Percent time below 3.9 mmol/L

These three endpoints will be tested in a hierarchical fashion in the order listed above. If C-peptide AUC is significant at  $\alpha=0.04$ , then they will be tested at  $\alpha=0.05$ . Otherwise, they will be tested at  $\alpha=0.01$ .

For all other secondary endpoints, the false discovery rate (FDR) will be controlled using the adaptive Benjamini-Hochberg procedure. The FDR will be calculated separately within each of the following categories:

- Secondary CGM Metrics
- Secondary Insulin Metrics
- Secondary HbA1c Metrics
- Secondary Clinical Metrics
- Subgroup Analyses and Sensitivity Analyses
- Per-Protocol Analyses
- Questionnaires

Due to the small number of subgroup analyses and sensitivity analyses, these will be combined into a single category. No adjustments for multiple comparisons will be done for safety outcomes.

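### The Poisson model for safety event counts allows for site but not for differences between children, so its p-values are too small if counts are overdispersed; the end of event counting also depends on the events

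*Combined protocol and SAP*

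**What the plan says.** SAP section 8 lists, among others, "Number of episodes of severe hypoglycemic events per subject and incidence rate per 100-person years" and "Number of episodes of DKA events per subject and incidence rate per 100-person years". Other adverse events and other serious adverse events are counts per subject, with no rate. Beside the episode counts stand subject-level outcomes such as "Number of subjects with severe hypoglycemic events", compared by logistic regression.

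For the rest the SAP says "For the count outcomes and the incidence rates, a Poisson regression model will be used", and "All models will adjust for site as a random effect". The DKA models also adjust for DKA at diagnosis. No participant-level term, dispersion parameter, robust variance, person-time offset or sparse-data method is named.

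The testing rule is "A p-value <0.05 will be used to declare statistical significance", two-sided under SAP 5.1, and SAP section 13 adds "No adjustments for multiple comparisons will be done for safety outcomes". Comparisons are made at 12 and 24 months, and at 36 and 48 months for those in the extension.

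Events enter from randomisation "until the last visit date or the last event date (whichever is later". Person-years are not defined. Protocol 11.2.1 closes adverse event reporting 3 weeks after participation ends. Protocol 14.5 names only repeated measures logistic regression for severe hypoglycaemia and ketone-positive hyperglycaemia.

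**The concern.** An episode count lets one child contribute several events. The protocol expects that this can happen: Protocol 9.15 lists recurrent severe hypoglycaemia and recurrent severe hyperglycaemia or DKA as grounds for withdrawal. If some children are more prone to episodes than others, counts vary more than a Poisson model allows. A site effect absorbs variation between sites, not between children within a site. The rate ratio stays unbiased, but its standard error is too small. A handful of children with several episodes could then yield a false safety signal against closed loop, or a false safety advantage for it.

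The counting rule is a second, smaller matter. A late event is included and extends follow-up to its date, while event-free time after the last visit is dropped. If person-years are computed to the same date, the rate is pushed upward.

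**Working it through.** **Inputs from the documents.** 48 per group (SAP 3, Protocol 14.7); two-sided 0.05 (SAP 5.1 and 8); 3-week reporting window (Protocol 11.2.1).

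**Assumed, because the documents give no values.** Mean events per child, m, from 0.05 to 2; gamma frailty between children with mean 1 and variance φ from 0 to 6.7; equal follow-up in both arms; no site effect or covariates.

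**Step 1: the plan's own figure.** None is stated for safety. The group size comes from the C-peptide calculation: n = 2 × (1.960 + 1.282)² × (0.18/0.126)² = 42.9, so 43 by the normal approximation; the t-test version gives 43.9, the SAP's 44. With 10% loss, 43/0.9 = 47.8, so 48.

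**Step 2: formula.** With frailty, the variance of a child's count is m(1 + φm), so variance/mean is V = 1 + φm. The Poisson standard error of the log rate ratio, √(1/A + 1/B) for A and B events in the two arms, takes V = 1 and is too small by a factor √V. With adequate counts the true type I error is about 2[1 − Φ(1.96/√V)]:

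- V = 1: 5.0%
- V = 2: 1.96/1.414 = 1.386, giving 16.6%
- V = 3: 1.96/1.732 = 1.132, giving 25.8%

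**Step 3: simulation.** 40,000 trials per setting, 48 per arm, no true difference; a trial with no events in one arm counts as no rejection. In the m = 0.3 row, m and V were set and φ = (V − 1)/m.

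| Mean per child | φ | V | Poisson Wald | Robust Wald |
|---|---|---|---|---|
| 0.05 | 0 to 5 | 1 to 1.25 | 0.1-0.5% | 0.1-0.3% |
| 0.1 | 0 to 5 | 1 to 1.5 | 1.7-4.8% | 1.9-3.0% |
| 0.2 | 1, 2, 5 | 1.2, 1.4, 2 | 6.1, 8.4, 13.4% | 5.1, 5.6, 6.3% |
| 0.3 | 3.3, 6.7 | 2, 3 | 15.2, 24.1% | not run |
| 1 | 0 | 1 | 4.8% | 5.4% |
| 1 | 1, 2 | 2, 3 | 16.6, 25.2% | 6.1, 6.8% |
| 2 | 1 | 3 | 25.4% | 5.9% |

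A second run at 0.2 per child gave 6.0, 8.0 and 13.9%. At 1 event per child with φ = 5 (V = 6), the Poisson Wald test rejects in 42.1% and the robust test in 8.1%.

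**Step 4: very sparse events.** At 0.05 per child (0.05 × 48 = 2.4 expected events per arm) the Poisson likelihood-ratio test rejects in 9.4% even with φ = 0, and 12.7% at φ = 5, while Wald rejects in 0.1-0.5%. That gap is mainly sparse data, not overdispersion. The SAP does not say which test will be used.

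**Step 5: end of follow-up.** Suppose person-time runs to the later of last visit (time T after randomisation) and last event, and events are picked up for a window w after the visit. The relative bias of the rate is about w/T, with w = 3/52 = 0.058 years:

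- T = 1.9 years: 0.058/1.9 = 3.0% (simulated 2.8-3.1%)
- T = 0.9 years: 0.058/0.9 = 6.4% (simulated 6.2-6.5%)
- T = 0.25 years, an early dropout: 0.058/0.25 = 23% (simulated 22-24%)

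The 0.9-year figure assumes that counting stops 3 weeks after the 12-month visit; the 3-week limit itself runs from the end of participation. With an assumed 3-month window the bias is 11-13% at T = 1.9 and 24-28% at T = 0.9. With the same T and reporting in both arms, the bias largely cancels in the rate ratio. With late reporting in one arm only and the 3-week window, the ratio shifts by roughly the same 3-6%.

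**The case against.** The strongest reply is that overdispersion is expected, not shown. Without heterogeneity and with adequate counts, the Poisson test holds about 5%. Protocol 11.3.2 calls severe hypoglycaemia a rare risk, and at 0.05-0.1 events per child the Wald test is conservative or near nominal. Variance/mean of 3 at a mean of 0.3 needs a frailty variance of 6.7, which is extreme. This stands: a reader might infer that 15-26% applies to severe hypoglycaemia and DKA, but the documents give no rates or dispersion that would support it.

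Second, the numbers of children with severe hypoglycaemia and with DKA are compared separately and are unaffected by repeats, so a result driven by a few children has a planned cross-check. No formal stopping guideline rests on these p-values (SAP 11). Both points stand, but the cross-check exists only for those two outcomes, not for other adverse events.

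Third, SAP 5.1 promises standard residual diagnostics for all analyses. This helps little: the remedies named there are transformation and nonparametric methods for skewed values, not overdispersed counts.

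Fourth, the counting sentence says which events are included; it does not define person-time. The follow-up bias is therefore conditional on person-years using the same date.

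Fifth, robust variance is not exact: at 1 event per child it still gives 6.1-8.1% for φ = 1 to 5. That is far closer to 5% than the 16.6-42.1% of the unadjusted Wald test.

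**Conclusion.** The point holds in conditional form. The count model makes no allowance for variation between children, so its p-values are anti-conservative if counts are overdispersed. Under the assumed ranges, type I error runs from 5% or less for rare events to 15-26% when variance/mean is 2-3. The concern is greatest for the more frequent events; other adverse events are the likely case, though their frequency is not stated either.

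A reader might go further and conclude that the planned safety p-values and rates are simply wrong. The documents do not support that: it depends on heterogeneity that they do not quantify, and the subject-level comparisons are not affected by repeat episodes. Nor can a rate error be claimed for other adverse events, since no rate is planned for them.

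The follow-up rule is a minor matter: about 3% upward at 24 months and 6% at 12 months in the severe hypoglycaemia and DKA rates, if person-time follows the same rule with a 3-week window. The bias is larger for early dropouts and mostly equal between arms.

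**What to change.** In SAP section 8:

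- Replace the count model by negative binomial regression, or by Poisson regression with participant-level robust variance, with log person-time as offset. Keep the site and DKA-at-diagnosis adjustments.
- Name an exact or permutation test, and the event total below which it replaces the model.
- Define person-years, and end both event counting and person-time at a date that does not depend on events: for example, the earliest of the analysis time point, withdrawal of consent, or the end of the adverse event reporting period.
- Align the safety methods named in SAP 8 and Protocol 14.5.

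The cost is SAP wording and a different model statement; no new data are needed. Intervals will be wider when events cluster in a few children.
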